## Abstract

Supplemental Digital Content is available in the text

## Introduction

1

Pulmonary rehabilitation is a cardinal component of chronic obstructive pulmonary disease (COPD) management.^[1,2]^ During the past decade, several prospective trials have shown that pulmonary rehabilitation in COPD patients was associated with a decrease in COPD-related handicap and an improvement of quality of life. In addition, a reduction of mortality was suggested in one of these studies when pulmonary rehabilitation was performed early after an acute COPD exacerbation.^[3,4]^ The pulmonary rehabilitation program includes individualized exercise training, therapeutic education, respiratory physiotherapy, help with smoking cessation, and nutritional and psychosocial coverage. Exercise training must include lower-limb training associated with upper-limb training. Indeed, many patients with COPD report difficulties in performing activities using upper limbs due to the dyspnea generated by these movements and upper limb fatigue.^[5–7]^ In addition, activities using upper limbs are performed at a lower intensity compared with healthy subjects.^[8]^ In COPD patients, the difficulties encountered in performing upper limb activities are partly related to respiratory disease, and in particular to the fact that the muscles required to mobilize the upper limbs are also required for ventilatory mechanics.^[6]^ Tangri and Woolf^[9]^ have shown that COPD patients have difficulties in activities of daily living (ADL) using upper limbs, especially for combing their hair, brush their teeth. They observed a modification of the respiratory pattern, breathing becomes rapid, shallow, and irregular.

Therefore, in activities involving upper limbs, patients with COPD report an increase in dyspnea. Upper limbs are used for 80% of daily life activities, upper limbs strengthening seems important to decrease dyspnea in patients with COPD.^[10]^

So, for these reasons, the authors of the recommendations about pulmonary rehabilitation propose to perform upper limbs muscle strengthening in patients with COPD.^[1]^ The objectives of this strengthening are to reduce dyspnea, improve quality of life, and improve strength and endurance of the upper limbs. However, the methods of muscle strengthening are not specified. The authors of a recent systematic review with meta-analysis^[11]^ report that during a pulmonary rehabilitation program, upper limbs exercise training decreases dyspnea, in comparison with no upper limbs exercise training. They mention that the modalities of strengthening are not clearly established, and they conclude that studies are necessary for clarifying modalities of strengthening in comparing upper limbs endurance strengthening versus upper limbs force strengthening.

The aim of this study is to compare the effects of upper limbs endurance strengthening versus upper limbs force strengthening, in patients with COPD during a pulmonary rehabilitation program.

## Methods/Design

2

### Setting

2.1

This prospective bi-center, open label randomized trial will be conducted in 2 pulmonary rehabilitation units.

### Population

2.2

Patients routinely admitted for a pulmonary rehabilitation program (4 weeks) in Centre Hospitalier des Pays de Morlaix (Morlaix, France) or in Centre Hospitalier Universitaire de Brest (Brest, France) will be included for the study if they had COPD stages from 2 to 4 (A–D) diagnosed according to GOLD criteria^[12]^ at admission (Forced Expiratory Volume in 1 second/Forced Vital Capacity < 0.7, Forced Expiratory Volume in 1 second < 80% of predicted value), if they are at least 18 years old, and if they sign consent form after receiving written information.

Non-inclusion criteria will be:

Patient with shoulder pain, shoulder osteoarthritis, or shoulder surgery.Previous pneumonectomy or lobectomy in the past 6 months.Refusal of participation.Patient with incapacity to follow a standard rehabilitation program.Pregnant or breast-feeding women.Patient under tutorship or curatorship.

### Study design

2.3

Participation in the study will be considered for all COPD patients admitted to the pulmonary rehabilitation department of the Centre Hospitalier des Pays de Morlaix or Centre Hospitalier Universitaire de Brest.

Eligible patients will be included after the investigator has provided complete oral and written information to the patients, completed the initial assessments for the pulmonary rehabilitation program, verified the inclusion and non-inclusion criteria, and obtained written consent form from patients.

The initial assessments for the pulmonary rehabilitation program include the following tests:

Spirometry with Forced Expiratory Volume in 1 second and Forced Vital Capacity maneuvers after bronchodilators (spirometry with plethysmography will be performed during the pulmonary rehabilitation program).Arterial puncture is performed for arterial blood gases analysis.Inspiratory muscle strength (PImax) is measured using a Micro RPM (Micro Medical, Rochester, UK).Exercise capacity is measured using 6-minute walk test (6MWT), 1-minute Sit to Stand test (1STST), and maximal cardiopulmonary exercise test on cycloergometer.Maximal voluntary quadriceps strength and quadriceps endurance are measured using a hand held dynamometer.^[13,14]^Dyspnea is evaluated according the recommendations^[15]^ with Dyspnea-12 questionnaire,^[16]^ Modified Medical Research Council dyspnea Scale,^[17]^ London Chest Activity of daily Living (LCADL),^[10]^ multidimensional dyspnea profile (MDP)^[18]^ at the end of the 6MWT.Quality of life is measured with Saint George Respiratory questionnaire (SGRQ)^[19]^ and COPD Assessment Test (CAT).^[20]^Anxiety and depression are evaluated using Hospital Anxiety and Depression Scale (HAD-A and HAD-D).^[21]^Fear of falling is evaluated using Fall efficacy Scale-International (FES-I)^[22]^Educational interview for therapeutic education program is performedConsultation for smoking cessation and/or consultation with a nutritionist is realized if necessary.

Others tests will be performed for this study:

The 6-minute Peg Board and Ring Test (6PBRT):Maximal voluntary strength of deltoid, biceps, and brachial triceps are measured using a hand held dynamometer.

### Randomization and allocation procedure

2.4

This study is a Randomized, open-label, bi-centre controlled trial in parallel groups distributed in a ratio (1:1) comparing upper limbs force strengthening (group F) to the upper limbs endurance strengthening (group E) during a pulmonary rehabilitation program in patients with COPD stages 2 to 4 (A–D).

Block randomization are performed with variable block sizes. Block sizes are randomly established by the statistician. Investigators will be kept blinded to each block size, to ensure that they could not become aware of patients’ allocation in advance.

After randomization, patients will be allocated to follow:

A 4 weeks pulmonary rehabilitation program with upper limbs force strengthening (group F).A 4 weeks pulmonary rehabilitation program with upper limbs endurance strengthening (group E).

Primary endpoint is open-label because it is an auto-questionnaire (LCADL). The other endpoints will be blinded evaluated, with an assessor, which will not participate to inclusion, randomization, nor pulmonary rehabilitation program.

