### Intervention

2.5

The standardized pulmonary rehabilitation program (both groups) will be conducted over 4 weeks, 5 days per week and will include aerobic exercise on a cycle ergometer and a treadmill (each for 30 minutes per day),^[9,10]^ strengthening of lower limb muscle groups, a therapeutic educational program, aerobic gymnastics in groups, a smoking cessation program, and sociopsychological and dietary advice.

Randomized intervention for group E:

In group E, patients will perform in addition to the classic pulmonary rehabilitation program, upper limbs endurance strengthening.

Details of upper limbs endurance strengthening:

It will be performed 3 times a week for 4 weeks, supervised by a physiotherapist. This strengthening is performed with dumbbells whose weight is determined according to the strength of the muscles of the upper limbs evaluated at the beginning of the program (at 30% of the maximum voluntary force).

Description of the exercises:

The patients have to realize 4 exercises. Patients are sitting on a stool.Exercise 1: upper limbs along the body => bending of the elbows then extending the elbows along the body.Exercise 2: hands to shoulders => extension of the elbows to the front then back of the hands to the shoulders.Exercise 3: hands to shoulders => elbow extension up, then hand back to shoulders.Exercise 4: upper limbs along the body => abduction of the upper limbs to the horizontal (elbows stretched), then back of the upper limbs along the body.Maximum 1-minute rest between each exercise.

Description of the sessions during the 4 weeks

Week 1:

Weight of the dumbbells at 30% of the maximum voluntary force.Perform 3 series of 10 movements for each exercise (exercise 1 to exercise 4).

Week 2:

Weight of the dumbbells at 30% of the maximum voluntary force.Perform 3 series of 15 movements for each exercise (exercise 1 to exercise 4).

Week 3:

Weight of the dumbbells at 30% of the maximum voluntary force.Perform 3 series of 20 movements for each exercise (exercise 1 to exercise 4).

Week 4:

Weight of the dumbbells at 30% of the maximum voluntary force.Perform 3 series of 25 movements for each exercise (exercise 1 to exercise 4).

Randomized intervention for group F:

In group F, patients will perform in addition to the classic pulmonary rehabilitation program, upper limbs force strengthening.

Details of upper limbs force strengthening:

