### Sample size calculation

2.7

A previous study^[29]^ (EMI2) reported a standard deviation of 10 points for the LCADL score. A 4-point improvement for LCADL during a pulmonary rehabilitation program would be clinically significant.^[24,25]^

With these assumptions, for an α-error of 5% and β-error of 10%, the expected sample size would therefore be 133 patients per group. In order to anticipate loss to follow-up or withdrawals of consent, 140 patients per group will be included, or 280 in total.

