### Statistical analysis

2.8

All the data will be collected by a research nurse blinded to treatment allocation. Continuous variables will be expressed as mean ± SD, as median (interquartile range) or frequency.

The mean's evolution for the endpoints obtained in each group will be analyzed using a Student *t* test or Wilcoxon test (in case of non-normal distribution) for within-group and between-group comparisons, respectively.

All data will be analyzed in an intention-to-treat analysis.

A *P*-value of <.05 will be considered statistically significant.

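### Two units recruit and treat, but the stated primary test has no centre term; adding centre is a small gain at almost no cost

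*Protocol article*

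**What the plan says.** Section 2.1 of the Protocol article sets out the structure: "This prospective bi-center, open label randomized trial will be conducted in 2 pulmonary rehabilitation units". Section 2.4 gives a 1:1 allocation and states "Block randomization are performed with variable block sizes". It adds that the statistician sets the block sizes and that investigators do not know them. No stratification factor is named, but the section does not say that one list serves both units either.

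Section 2.8 names the analysis. The change in each endpoint "will be analyzed using a Student *t* test or Wilcoxon test (in case of non-normal distribution) for within-group and between-group comparisons". Neither centre nor any other covariate appears.

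On delivery, Section 2.5 says "The standardized pulmonary rehabilitation program (both groups) will be conducted over 4 weeks, 5 days per week". The upper-limb sessions are described in the same words for both arms: "It will be performed 3 times a week for 4 weeks, supervised by a physiotherapist".

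Section 2.7 sizes the trial. A previous study "reported a standard deviation of 10 points for the LCADL score", and the target is 4 points. With an alpha of 5% and a beta of 10% this gives 133 per group, raised to 140 per group (280 in total) for losses.

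**The concern.** Patients come from two hospitals, one general and one university. LCADL change may differ between them through case mix or local delivery, although the article gives no data on this. The named test leaves any such difference in the error term.

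The consequence depends on how the lists were built, which the article does not report:

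- **Pooled lists.** The arms can differ by chance in their centre mix, and neither design nor analysis corrects for it.
- **Lists by centre.** The design balances centre, but the test computes its standard error as if it had not. The result is a test slightly stricter than 5%.

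What is at stake in both cases is precision, not validity.

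**Working it through.** **Inputs from the documents.** Target 4 points, SD 10, alpha 5%, power 90%, 133 per arm before losses (Section 2.7); two centres (Section 2.1).

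**Assumptions.** The documents give no centre difference and no centre split. I take a difference in mean LCADL change of D = 2, 4 or 6 points and a share p = 50% or 30% for one centre. The SD of 10 is treated as the total SD of the analysed change across both centres.

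**Step 1: the plan's own figure.** n = 2 × (1.960 + 1.282)² × 10² / 4² = 131.4, so 132 per arm by the normal approximation. The noncentral t gives 133 (power 90.1%), so the stated 133 reproduces with a two-sided test. By the normal approximation at 133 per arm, SE = 10 × √(2/133) = 1.23 and power = Φ(4/1.226 − 1.960) = Φ(1.302) = 90.4%. This is the reference value below.

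**Step 2: centre in the model.** With the total SD held at 10, the within-centre SD is w = √(100 − p(1 − p)D²). For p = 50% and D = 6, w = √(100 − 9) = 9.54. Replacing 10 by w gives the required n and the power at 133 per arm.

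**Step 3: pooled lists, no adjustment.** With 133 per arm, the hypergeometric SD of the between-arm difference in centre share is 0.061 (p = 50%) or 0.056 (p = 30%). The 95% range is 1.96 times this, about ±12 or ±11 percentage points. Multiplying by D gives the chance shift in the treatment contrast.

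**Step 4: lists by centre, no adjustment.** The difference then has true standard error w√(2/133), but the test uses 10√(2/133). The effective critical value is 1.96 × 10/w. For p = 50% and D = 6 it is 2.05, so the type I error is about 4.0%.

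| p | D | w | n per arm, adjusted | Power at 133, adjusted | Chance shift, pooled lists (95%) | Type I error, lists by centre, unadjusted | Power, lists by centre, unadjusted |
|---|---|---|---|---|---|---|---|
| 50% | 2 | 9.95 | 131 | 90.63% | ±0.24 | 4.89% | 90.46% |
| 50% | 4 | 9.80 | 127 | 91.45% | ±0.48 | 4.55% | 90.80% |
| 50% | 6 | 9.54 | 120 | 92.78% | ±0.72 | 3.99% | 91.38% |
| 30% | 2 | 9.96 | 131 | 90.59% | ±0.22 | 4.90% | 90.45% |
| 30% | 4 | 9.83 | 127 | 91.28% | ±0.44 | 4.62% | 90.73% |
| 30% | 6 | 9.61 | 122 | 92.40% | ±0.66 | 4.15% | 91.21% |

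**Step 5: reading the table.** Against the 90.4% reference, adjustment adds about 0.2 to 2.4 percentage points of power. If the lists are kept by centre, the unadjusted test already has slightly more than 90.4%. The gain is then smaller: from 90.59 − 90.45 = 0.14 to 92.78 − 91.38 = 1.40 points.

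The largest chance shift in the table, 0.72 points, is 0.72/1.23 = 0.59 of a standard error. At D = 4 the shift is 0.48/1.23 = 0.39 of a standard error.

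**The case against.** The strongest reply is that nothing here is an error. An unadjusted test is valid after unstratified randomisation, because the standard error already covers chance imbalance. After stratified randomisation it errs on the safe side. The stated sample size reproduces, so the trial is not short of power because of centre. The article reports no difference between the units, and it describes a standardised programme with common eligibility. Covariates are also often left to an analysis plan. All of this stands as to validity and size. It does not remove the point, because Section 2.8 is not silent on method. It names a test, and a slightly better one is available at almost no cost.

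Three stronger readings are tempting, and the documents do not support them:

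- **Allocation was not stratified by centre.** Section 2.4 neither states nor denies stratification. Separate blocked lists for each unit would fit its wording equally well, and a condensed article may leave that detail to the full protocol.
- **Unequal centre mix biases the treatment effect.** Under randomisation any imbalance is chance variation, and the shifts in the working are edges of a 95% range multiplied by an assumed centre difference.
- **Physiotherapist delivery makes centre a serious confounder.** Supervision is worded identically in both arms, and nothing ties a therapist to an arm.

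**Conclusion.** The point holds as a minor efficiency matter. The stated analysis omits centre in a two-unit trial. This costs a little precision if the lists are pooled, and it makes the test slightly conservative if they are kept by centre.

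For assumed centre differences of 2-6 points, adjustment takes power at 133 per arm from about 90.4% to 90.6-92.8%. Put in patients, the required number falls from 132 per arm to 131 at the low end and to 120-122 at the high end. The high-end saving of 10-12 per arm exceeds the 7 per arm (140 − 133) that the plan adds for losses. The low-end saving is a single patient.

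These figures rest on the assumed centre difference and split, and on reading the SD of 10 as the total SD of the analysed change. If the centres do not differ, there is essentially no gain and essentially no loss.

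**What to change.** In Section 2.8, make the primary between-group comparison a linear model of LCADL change with arm and centre as fixed effects. Report the adjusted arm difference with its 95% confidence interval. If the rank-based fallback is used, replace the plain Wilcoxon test by a centre-stratified one (van Elteren). Fix this in writing before any outcome is compared by arm.

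Leave the allocation lists as they are. The change works whether they are pooled or kept by centre, so it does not disturb a running trial.

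The cost is one covariate already known for every patient and one model degree of freedom. It needs no extra patients, visits or staff.

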#### Primary outcome

2.6.1

London Chest Activity of daily Living questionnaire (LCADL).^[10]^

This 15-item, self-administered questionnaire has been developed by Garrod et al.^[10,23]^ It allows an evaluation of dyspnea in patients with COPD during daily activities divided into 4 components: self-care, domestic, physical, and leisure. Patients could score from 0: “I would not do anyway” to 5: “I need someone else to do this.” LCADL score is calculated by aggregating the points assigned to each question (0–75), with a higher score representing maximal disability. MID has been determined for LCADL.^[24,25]^ A decrease of 4 points during a pulmonary rehabilitation program is clinically important for patients.

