#### Secondary outcomes

2.6.2

Dyspnea will be also assessed with other scales: Modified Medical Research Council dyspnea scale^[17]^ and Dyspnea-12 questionnaire which allows to assess sensory and emotional components of dyspnea.^[16,26]^

The 6-minute Peg Board and Ring Test (6PBRT):

The 6PBRT is a good test to evaluate upper limbs exercise capacity in COPD patients, and Takeda et al^[27]^ showed a correlation between 6PBRT score and physical activity. In our study, we will use 6PBRT as a functional marker, in order to measure upper limbs endurance.The 6PBRT was performed according to the method of Zhan et al,^[28]^ with a slight modification.

Patients sit in a chair and a pegboard with multiple peg positions is placed in front of the subject at arm's length from the body. Two pegs are positioned at the shoulder level and 2 at 20 cm above the shoulder level, and 5 rings (Zhan used 10 rings) (15 g per ring) are put on each of the 2 lower pegs. Patients are instructed to use both hands simultaneously to move 1 ring from each of the lower pegs to the upper pegs: subjects need to use the left hand to move the ring on the left lower peg, and the right hand to move the ring on the right lower peg. After all 10 rings are moved from the lower pegs to the upper pegs, patients move again 1 ring from each of the upper pegs back to the lower pegs. Before the test, patients are allowed to do 1 cycle of moving up and down as a practice to familiarize themselves with the procedures. At the signal “go,” subjects need to move as many pegs as possible during 6-minute. The final score is the total number of rings moved during the 6-minute period. Subjects are permitted to stop and rest during the test if they feel severe dyspnea, fatigue, or other discomfort, and continue moving the pegs as soon as they can. The patient is encouraged every minute using the standard phrases used during the 6MWT.

Subjects were asked to score the perceived dyspnea and upper limb fatigue before and at the end of the test by using Borg scale. Each patient will perform the 6PBRT twice. A pulse oximeter will be used to monitor heart rate (HR) and pulse oxygen saturation (Spo2) at the beginning and at the end of the test.

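### Section 2.4 claims blinded evaluation for every endpoint except LCADL, but mMRC and Dyspnea-12 are also ratings by patients who know their arm

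*Protocol article*

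**What the plan says.** Section 2.1 (Setting) declares the design: "This prospective bi-center, open label randomized trial will be conducted in 2 pulmonary rehabilitation units". Section 2.4 (Randomization and allocation procedure) also calls the trial open-label. No masking of patients is described anywhere in the article.

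Section 2.4 then separates the endpoints into two classes. For the first it says "Primary endpoint is open-label because it is an auto-questionnaire (LCADL"), which fits section 2.6.1, where LCADL is called a self-administered questionnaire. For the second it says "The other endpoints will be blinded evaluated, with an assessor, which will not participate to inclusion, randomization, nor pulmonary rehabilitation program". No exception is made within that second class.

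Section 2.6.2 (Secondary outcomes) opens with two further dyspnea instruments: "Dyspnea will be also assessed with other scales: Modified Medical Research Council dyspnea scale", and the "Dyspnea-12 questionnaire which allows to assess sensory and emotional components of dyspnea". It then describes the 6PBRT, scored as the number of rings moved in six minutes, and maximal voluntary strength of deltoid, biceps and triceps by handheld dynamometer.

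Section 2.8 (Statistical analysis) adds a statement about data handling: "All the data will be collected by a research nurse blinded to treatment allocation".

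**The concern.** The protocol gives its own test for when an endpoint is open-label: the patient is the one who supplies the score. It applies the test to LCADL and then stops, although two of the secondary outcomes meet it as well. For those two, the document states a blinding property that the design cannot deliver.

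What is at stake is interpretation. Dyspnea is the construct of the primary outcome, and mMRC and Dyspnea-12 measure the same construct. Any influence that knowing the arm has on how a patient answers LCADL can act on these two scales in the same way. If they are taken as blinded, on the strength of section 2.4, they are given more evidential weight than they have. Agreement between them and LCADL says nothing about whether knowledge of the arm affected the answers.

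**Working it through.** The plan states no figure on this point, so the check is a comparison of sections.

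**Step 1. Do patients know their arm?** Sections 2.1 and 2.4 call the trial open label. Section 2.5 describes visibly different regimens. Group E trains at 30% of maximum voluntary force throughout, rising from 3 series of 10 to 3 series of 25 movements per exercise. Group F trains at 60% to 80%, with 2 and later 3 series of 10. In week 4 that is 3 × 25 = 75 movements per exercise against 3 × 10 = 30. With no masking described, the patient must be taken to know the arm.

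**Step 2. What is the protocol's criterion?** Section 2.4 makes LCADL open-label for one stated reason: the patient completes it. The criterion is who gives the rating.

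**Step 3. Apply the criterion to each outcome named in section 2.6.2.**

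| Secondary outcome | Source of the score | Blinding claimed in 2.4 | Can a blinded assessor deliver it? |
|---|---|---|---|
| mMRC dyspnea scale | patient's own rating | blinded | no |
| Dyspnea-12 | patient's own answers | blinded | no |
| 6PBRT | rings counted by assessor | blinded | yes, for the count |
| Muscle strength | dynamometer read by assessor | blinded | yes, for the reading |

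The article does not state that mMRC and Dyspnea-12 are patient-reported. It follows from what it does say: one is a dyspnea scale, the other a questionnaire on sensory and emotional components of dyspnea. The 6PBRT and the strength test still depend on patient effort, so assessor blinding there covers counting, reading and encouragement but not motivation.

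**Step 4. Count.** With strength taken as one outcome, the claim fails for 2 of 4 named secondary outcomes. If the three muscles are counted separately, it fails for 2 of 2 + 1 + 3 = 6. The two outcomes concerned are the same either way. Other patient questionnaires, such as SGRQ, CAT and HAD, appear in section 2.3 as initial assessments and not in section 2.6.2, so they are not counted.

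**Step 5. Compare section 2.8 with section 2.4.** Section 2.8 concerns who collects the data, and section 2.4 concerns who rates. A nurse unaware of allocation can collect a form that an unblinded patient has filled in, so both statements can be true. Section 2.8 does not say that collection is all its blinding covers.

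**The case against.** The best defence is that section 2.4 promises assessor blinding and nothing more. The trial is openly declared open label, and only LCADL is called self-administered. mMRC and Dyspnea-12 could be administered by interview, in which case an independent, blinded assessor would indeed be involved. That reading is possible and makes the sentence imprecise more than false. It does not rescue the claim. The patient still supplies the answer, and a reader who sees LCADL set apart as open-label will take the remaining endpoints to be free of that limitation.

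A second objection is that bias is not demonstrated. Both arms receive supervised training with the same four exercises three times a week, and the Discussion says evidence is lacking to recommend either modality. No direction of expectation follows from the document. This stands, and no direction or size of bias is claimed here.

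Four stronger readings are tempting and are not supported:

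- A reader might infer that section 2.8 contradicts section 2.4, since it speaks of all data being collected blind while LCADL is open-label. The two concern different people and can coexist, so only a clarification is needed.
- A reader might add the Borg scores, since "Subjects were asked to score the perceived dyspnea and upper limb fatigue before and at the end of the test by using Borg scale". But the final 6PBRT score is the ring count, and the only use the document gives for these dyspnea and fatigue ratings is to check recovery between the two test runs. They are not named as endpoints, so they are not counted as mislabelled.
- A reader might infer that the sponsor intends to present the secondary scales as blinded corroboration of LCADL. No section says so. The wording would permit it, which is a reason to correct it, but no such plan is shown.
- A reader might want any dyspnea benefit to be interpreted jointly with the 6PBRT because its count can be blinded. The protocol uses that test as a measure of upper-limb endurance, which one arm specifically trains. It neither confirms nor refutes a dyspnea effect, and no error in the document calls for such a rule.

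**Conclusion.** The point holds in a narrow form. The blinding statement in section 2.4 is wrong as worded for mMRC and Dyspnea-12, two of the four named secondary outcomes. By the protocol's own reasoning they are open-label, whoever administers them. The statement remains tenable for the 6PBRT ring count and dynamometer strength.

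This rests on two assumptions. The first is that patients know which regimen they follow, which the open-label declaration and the description of the arms support. The second is that mMRC and Dyspnea-12 are answered by the patient, which their descriptions imply.

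Severity is minor. The open-label status of the primary endpoint is already disclosed, and the sample size of 133 per group (140 with the allowance for losses) does not depend on this. What changes is how the secondary dyspnea scales may be described and weighed when results are reported.

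**What to change.** In section 2.4, replace the blanket statement with two explicit classes. LCADL, mMRC and Dyspnea-12 are patient-reported and open-label. The 6PBRT ring count and dynamometer strength are measured by an assessor blinded to allocation who takes no part in inclusion, randomization or rehabilitation. Do not report mMRC or Dyspnea-12 as blinded evidence.

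In section 2.8, add a clause saying that the nurse's blinding concerns data collection and does not make patient-reported outcomes blinded.

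The change is wording only. It alters no visit, measurement, sample size or analysis. The cost is a less favourable blinding claim for the secondary dyspnea outcomes.
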